#### **4.3 Exclusion criteria**

A potential subject who meets any of the following criteria will be excluded from participation in this study:

- Severe disability (e.g. neurological, orthopedic, cardiovascular) according to the investigator, pregnancy or serious concurrent illness that might interfere with surgery or follow-up.
- Active additional neuro-otologic disorders that may mimic MD (e.g. vestibular migraine (VM), recurrent vestibulopathy, phobic postural vertigo, vertebro-basilar TIAs, acoustic neuroma, congenital disorders, enlarged vestibular aqueduct (EVA)-like or genetic disorders (like DFNA9), cervicogenic dizziness), based on the complete clinical record.
- Previous ear surgery for MD (IT injection is not an exclusion criterion)
- Language difficulties
- Active otitis media (with or without effusion)
- Unable or unwilling to use DizzyQuest App

- Unable to undergo MRI (such as gadolinium allergy, claustrophobia, implanted non-MRI compatible device of material, BMI)
- Deafness of the contralateral ear

- Rationale inclusion and exclusion

We aim to perform surgery only on patients with an active Ménière's disease. Because both procedures involve surgery with its associated risks, we only want to perform surgery on participants who have had no benefit of conservative medical therapy and IT injection. Moreover, this will reflect the group of patients who will undergo this surgery in usual clinical practice if this trial leads to EDB being a standard procedure. Patients with prior non-ablative surgery like ESD are excluded in order to avoid any influence in the end result. Moreover, we aim to eliminate or at least minimize all factors that might interfere with follow-up. Patients with contralateral deafness are excluded because it is not clear what the effect of EDB on hearing function is.

#### 4.4 Sample size calculation

The sample size for this RCT was computed using software package PASS 11. The sample size calculation is based on the study performed by Saliba (Saliba 2015), in which complete control of vertigo was reached in 96,5% of the patients who underwent EDB. According to literature, endolymphatic sac decompression is effective in  $\pm 70\%$  of the patients (Brinson 2007, Convert 2006, Durland 2006).

We compare MD participants undergoing an operation with clip (EDB group: A group) independently with MD participants undergoing operation without clip (decompression group: B group). Null hypothesis is that the percentage points difference between groups is nil ( $p_A = p_B$ ), with two-sided alternative hypothesis ( $p_A \neq p_B$ ) and with anticipated 25% percent difference ( $p_A = 95\%$  and  $p_B = 70\%$ ). Power is at least 80%. The chance of a false positive finding for either of the analyses is controlled at the 5% level (family wise error rate). To obtain a power of at least 80% for Fisher's Exact test, the required sample size is 32 in groups A and B (allocation ratio = 1). Loss to follow-up will likely occur in a small percentage of cases ( $n=5$  per arm). No selective loss to follow-up is anticipated and a missing-at-random assumption seems reasonable. Missing outcomes will therefore be imputed using multiple imputation in the main analysis. Two sensitivity analyses will be conducted as well, where missing outcomes will be treated as failures or success, respectively. In this case the sample size would be 37 in group A and B (allocation ratio = 1). The total number of participants would be 74.

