Recently, an international guideline for the diagnostic work-up and treatment of MD was published (Basura 2020). It recommends step-up treatment, starting with education of patients and discussing diuretics/betahistine. IT corticosteroids are considered optional if patients do not respond to more conservative therapy. A last non-ablative option that can be considered, is endolymphatic sac decompression, however, results from this type of surgery are discordant. If there is no response to non-ablative treatments, treatment with intratympanic gentamicin is recommended, and if the disease remains unmanageable and the patient has nonusable hearing, labyrinthectomy is advised. Patients should also be referred for vestibular rehabilitation therapy in case of chronic balance problems, and clinicians should counsel patients with hearing problems about hearing assistive technology.

In the Netherlands, there are currently no specific guidelines for the treatment of MD. The guideline 'Dizziness in Elderly' of the Dutch ENT Society ('Duizeligheid bij ouderen', NVNKO, 2015) advises to refer the patients to a specialized ENT surgeon. The guidelines 'Dizziness' of the Dutch General Practitioner Society (Bouma 2017) for general practitioners also advises to refer the patient to an ENT surgeon, but only in case of rapid progressive hearing loss or additional complaints such as instability, head ache or persisting tinnitus. There is no guideline from the Dutch ENT society regarding Meniere's disease.

- Endolymphatic sac surgery

Other surgical treatment techniques target the endolymphatic sac (ES). The advantage of these procedures is that they are non-destructive and do therefore not affect the cochlear and vestibular function, thereby preserving hearing and balance. These procedure involve decompression, shunting or drainage of the ES.

Endolymphatic sac decompression (ESD) consists of a mastoidectomy and, after identification of the endolymphatic sac, wide decompression of this structure (Sennaroglu,

2001). ESD has few surgical complications in comparison with the ablative surgery mentioned above. There is no consensus on the effect of decompression. Convert et al (Convert 2006) report improved quality of life after decompression in a case study of 90 subjects after a follow up period of 57.5 months on average.

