Drainage or shunting of the endolymphatic sac (ESS) involves identification of the ES, followed by incision of the sac. A shunt is then placed, enabling drainage of the endolymph. There are several studies that were directed to investigate the effectiveness of ESS (Bretlau 1989, Thomsen 1998, Brinson 2007). Bretlau and Thomsen compared ESS to a sham operation; no differences between the groups was observed. Brinson compared ESS to ESD performed on 88 and 108 patients, respectively. He concluded that both procedures are effective

Multiple histological studies refute the rationale of endolymphatic sac surgery. Firstly, Chung et al (2011), performed a histopathological study 15 patients who had undergone ESS. If the endolymphatic sac does indeed have a function in resorption of the endolymph but does so inadequately, ESS and especially ESD would allow expansion of these structures and would therefore diminish hydrops. However, diffuse hydrops on temporal bone was seen in the cochlea, the saccule, the utricle, and the ampulla after ESD. The authors conclude that ESD does not relieve hydrops in patients with Ménière's disease.

In addition, if the ES was responsible for endolymph resorption, an increase of hydrops can be expected after amputation of the ES. However, Linthicum et al. (2011) reported a case in which removal of the ES did not lead to an increase of hydrops, as seen on temporal bone histopathology. In the assessed samples, Reissner's membrane was attached to the spiral ligament in a normal way, without any evidence of hydrops in the cochlea. In conclusion, the role of the ES is not merely absorption of the endolymph and therefore, providing more space to allow dilatation is not the solution for the observed hydrops.

The success rates of these surgical interventions vary between 30-95% (Sennaroglu 2001; Huang 1991; Silverstein 1989, Durland 2005, Pullens 2013; Convert 2006). It should be noted that the natural course of MD is also favourable, and it cannot be determined to what extent this outcome is due to the surgical intervention. Moreover, the placebo effect may play a major role in the relief of complaints, as 70% of MD patients in all groups (all surgical interventions as well as the control groups) experienced some relief of complaints. This either implicates a beneficial effect of any surgical intervention or of any intervention, be it surgical or non-surgical. This was earlier suggested by Thomsen (Thomsen 1981).

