This operation, referred to as the Endolymphatic Duct Blockage (EDB), involves placing a clip on the endolymphatic duct to separate the endolymphatic sac from the vestibulum and

the rest of the inner ear. Blockage of the endolymphatic duct impedes accumulation of endolymph in the inner ear, and therefore of vertigo attacks. Benefits of this technique are its permanent nature and the fact that it does not destroy the labyrinth or inner ear function.

Saliba (Saliba 2015) has performed a randomized trial to study the effect of EDB. The trial compared EDB to ESD and was conducted prospectively and non-blinded. There was no comparison to a group of patients receiving placebo treatment, for instance a sham operation. The results have been published in 2015 (Saliba 2015) and show that 34 of 35 treated patients were free of vertigo attacks after EDB surgery. It is interesting to note that the efficacy for the absence of vertigo attacks following ESD was only reported to be about 40% in Saliba's trial (Saliba 2015). In earlier studies by Bretlau and later Thomsen, percentages for both ESD and sham operations were reported to be as high as 70%. Possibly, this can be explained by the open character of the Saliba study, causing patients to experience the 'nocebo-effect', caused by feeling like they have not been treated because they did not have the EDB surgery (but the ESD instead). The fact that Saliba et al. did not assess outcomes in a double-blinded way is a fatal flaw in methodology given the high placebo effect of interventions in Ménière disease. Moreover, randomisation was not stratified and there is a risk of recall bias, as it is not described how vertigo bouts are recorded. Lastly, all participants were asked to follow the CATS (caffeine, alcohol, theophylline and salt restricted diet). The role of this diet is not clear.

In a more recent publication by the group of Saliba (Gabra 2016) it is reported that 43 (79%) of a group of 54 patients treated with EDB had an improved quality of life (QoL). The results of these studies indicate that EDB may have a favourable effect on both the bouts of vertigo that MD patients suffer, as on the quality of life.

It should be noted that this study was at risk for recall bias, as patients had to fill out questionnaire in retrospect.

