### 3. STUDY DESIGN

The EDB trial is designed as a multicentre, randomized, double blind trial to compare the effectiveness of EDB surgery with decompression surgery in number of patients who are free of vertigo attacks at 12 months follow-up.

- Duration of the study

Total duration of the study is 4 years. In the first 6 months the study will be started, followed by a 2-year period for inclusion and another year for follow up. Analysis of the results will take 6 months. One year after surgery of the last included patient, randomization can be unblinded. In case of a favourable result of EDB, patients in the decompression group will be offered re-surgery to perform EDB if they still suffer attacks. This surgery will be performed within one year after deblinding. In case of a favourable outcome a trajectory for implementation in the current Dutch health care system is also foreseen. Within six months after completion of the study, Zorginstituut Nederland (ZIN) will evaluate the results and decide if the intervention should be implemented in Dutch health care.

- Justification of the design

Three initiating centres (ICs) and four participating centres (PCs) will include patients. A large number of participating centres is chosen to enable rapid inclusion of the required number of participants. As the study ends one year after surgery of the last participant included, it is important to limit the time between surgery of the first participant and last participant. This so to be able to offer the EDB to the decompression group participants who still suffer attacks within a reasonable time span in case of an outcome favourable for EDB. The multicentre design of the study facilitates fast adoption and dissemination of the surgical technique in case of a favourable outcome of EDB.

Endolymphatic sac decompression was chosen as control intervention because the procedure is very similar to EDB. When performing EDB, the same area is exposed and decompression to allow placement of the clip. Because there is no consensus about the effectiveness of decompression, research on this intervention is justified.

The placebo effect plays an important role in the treatment of MD; 70% of the patients experience improvement after any surgical intervention (Thomsen 1981, Bretlau 1989, Thomsen 1998, Pullens 2013). However, because the interventions are equal in intensity, i.e. surgical treatments. Therefore we do expect similar placebo effects in the groups.

- Flow chart

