#### 4.5 Numbers needed to treat

The number needed to treat (NNT) is an epidemiological measure used in communicating the effectiveness of a health-care intervention. The NNT is the average number of patients who need to be treated to prevent one additional bad outcome (e.g. the number of patients that need to be treated for one of them to benefit compared with a control in a clinical trial). For this study: NNT A vs B:  $100/(p1-p2) = 100/(95\%-70\%) = 100/25 = 4$

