## 8. METHODS

### 8.1 Study parameters/endpoints

#### 8.1.1 Main study parameter

The main study parameter is the number of patients free of vertigo attacks at 12 months after surgery. This parameter was chosen because vertigo is the most invalidating symptom of MD.

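### Section 4.4 takes its 70% control rate from an undefined measure of effectiveness, so the single claim of at least 80% power is not supported on the attack-free endpoint

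*Protocol*

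**What the plan says.** Section 8.1.1 sets the endpoint: "The main study parameter is the number of patients free of vertigo attacks at 12 months after surgery". Section 4.4 then builds the sample size from two rates.

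- **EDB arm.** In the earlier EDB trial, "complete control of vertigo was reached in 96,5% of the patients who underwent EDB". The calculation uses 95%.
- **Control arm.** "According to literature, endolymphatic sac decompression is effective in" about 70% of patients, citing three decompression papers. No outcome or time point is given.

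The anticipated difference is 95% minus 70%, or 25 points. Section 4.4 claims at least 80% power for a two-sided Fisher's exact test with 32 per arm, raised to 37 per arm (74 in total) for losses. Section 10.1 plans a chi-square test or Fisher's exact test.

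The 70% figure recurs under other labels:

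- Section 1 (endolymphatic sac surgery): "as 70% of MD patients in all groups (all surgical interventions as well as the control groups) experienced some relief of complaints".
- Section 3 (justification of the design): "70% of the patients experience improvement after any surgical intervention".
- Section 11.4: an estimated 70% of the decompression group will benefit.

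Section 1 says that one of the three papers cited in 4.4 did "report improved quality of life after decompression in a case study of 90 subjects", at a mean follow-up of 57.5 months. On the endpoint itself, Section 1 (endolymphatic duct blockage) says of the earlier EDB trial that "the efficacy for the absence of vertigo attacks following ESD was only reported to be about 40" per cent. Section 4.5, beginning "For this study: NNT A vs B", uses 95% and 70% to give a number needed to treat of 4.

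**The concern.** For a binary endpoint the two assumed rates fix both the difference and the variance, so they must measure the same outcome. Section 4.4 labels the EDB rate as complete vertigo control and leaves the control rate undefined. Most other uses of 70% in the protocol describe something looser than freedom from attacks. The one explicitly attack-free figure for decompression, about 40%, comes from the same trial that supplies the EDB rate, and 4.4 neither uses it nor explains why not.

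The sample size, the power claim, the number needed to treat and the benefit statement to the ethics committee all rest on this rate. If it is on another scale, the stated power does not describe the test that will be run on the primary endpoint.

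**Working it through.** **Inputs.** Two-sided 5% level, equal arms, 32 per arm (37 before losses), rates of 95% and 70% (section 4.4); about 40% attack-free after decompression (Section 1). Control rates of 50% and 60% are assumed values that fill the range between 40% and 70%.

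**Method.** Exact power is the sum, over all outcomes *i* (EDB) and *j* (control), of Bin(*i*; n, pA) × Bin(*j*; n, pB), counting only the tables that the test rejects. This was done for the two-sided Fisher test and for the uncorrected Pearson chi-square.

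**Step 1: the plan's own figure.** At 95% v 70%, Fisher power is 68.0% at 32 per arm and 77.6% at 37. It first reaches 80% at 39 per arm (80.7%; 79.2% at 38). The uncorrected chi-square gives 80.6% at 32 and 86.1% at 37. So 32 per arm matches the chi-square and not the Fisher test that 4.4 names. This shortfall holds whatever the 70% measures.

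**Step 2: vary the control rate.** A new control rate changes the variance, and it also changes the difference unless the EDB rate moves with it. Both cases are shown (Fisher / chi-square).

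| EDB v control | Difference | 32 per arm | 37 per arm |
|---|---|---|---|
| 95 v 70 (plan) | 25 | 68% / 81% | 78% / 86% |
| *25-point gap kept* | | | |
| 85 v 60 | 25 | 53% / 63% | 60% / 69% |
| 75 v 50 | 25 | 46% / 56% | 51% / 60% |
| 65 v 40 | 25 | 45% / 56% | 48% / 58% |
| *EDB kept at 95%* | | | |
| 95 v 60 | 35 | 92% / 96% | 96% / 98% |
| 95 v 50 | 45 | 99% / over 99% | over 99% / over 99% |
| 95 v 40 | 55 | over 99% / over 99% | over 99% / over 99% |

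**Step 3: why the gap-kept rows fall.** The sum of binomial variances is 0.95 × 0.05 + 0.70 × 0.30 = 0.2575 at 95 v 70. At 65 v 40 it is 0.65 × 0.35 + 0.40 × 0.60 = 0.4675. The ratio is 0.4675 / 0.2575 = 1.82, so the same 25 points is harder to detect away from the ceiling.

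**Step 4: number needed to treat.** It is 100 divided by the difference in points: 100/25 = 4 wherever the gap is kept. With EDB at 95% it is 100/35 = 2.9, 100/45 = 2.2 and 100/55 = 1.8 at control rates of 60%, 50% and 40%.

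**The case against.** A reader might infer that the 70% is a relief rate and that the trial is therefore underpowered. The documents do not support either step.

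- **What the 70% measures is open.** Section 4.4 does not define effectiveness, and the relief and improvement sentences do not cite its three papers. The quality-of-life description of one of those papers attaches no percentage and does not exclude a vertigo-control rate. Section 1 also sets a figure as high as 70% directly against the 40%, as if on one scale. Only the cited papers could settle this.
- **The direction is not fixed.** The 25 points is simply 95 minus 70, and it is not presented as a minimal important difference. With EDB held at 95%, a lower control rate raises power, and 70% is then the cautious choice. The low figures need an EDB rate of 65% to 85%, which no section proposes.
- **The 40% is discounted with reasons.** It comes from an unblinded trial with a possible nocebo effect. A higher control rate is arguable for a blinded trial with a strong expected placebo response.

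All three points stand, and they limit the concern. They do not remove it. Section 4.4 does not make the nocebo argument, and Section 1 calls the lack of blinding in that trial a fatal flaw, so its EDB rate is not secure either. Nor can it be said in advance that a null result would fail to exclude 25 points, because that depends on the observed confidence interval.

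**Conclusion.** The concern holds in limited form. The 70% control rate is not shown to be an attack-free rate, and a single claim of at least 80% power is not supported. At 32 per arm, Fisher power runs from about 45% (65% v 40%) to over 99% (95% v 40%), depending on which of the two rates moves. At the plan's own rates it is 68%, or 77.6% with all 37 per arm analysed.

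The range rests on the protocol's figures of 40% and 70% as its ends and on two assumptions about the EDB rate. It does not show that the true control rate is 40% or that the trial is too small. The fault lies in an undefined input and in a power statement that fails for the test it names.

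**What to change.** Keep N at 74 and change the text as follows.

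- **Section 4.4, control rate:** state which outcome and time point the 70% measures, and justify an attack-free control rate against the protocol's own figure of about 40%. If nocebo is the reason for setting the 40% aside, say so there.
- **Section 4.4, power:** name one primary test, and match section 10.1 to it. Replace the 80% claim with power for that test over control rates of 40% to 70%, both with the 25-point gap kept and with EDB at 95%. State that the Fisher test named there has 68% power at 32 per arm and 77.6% at 37, at 95% v 70%. For Fisher, do not say that 25 points is adequately powered even at 70%.
- **Section 4.5:** give the number needed to treat over the same range.
- **Section 11.4:** say which outcome the 70% benefit statement refers to.

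The cost is rewording, with no extra patients or procedures. The downside is a less favourable power statement.

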#### **8.5 Replacement of individual subjects after withdrawal**

The number of participants (as mentioned in chapter 3) takes into account that at least 15% of the participants in both arms of the study will drop out. We therefore do not expect to replace participants.

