### 10.1 Primary study parameter

The primary outcome is defined as being attack free at 12 months follow-up. The required significance level of findings ( $\alpha$ ) will be equal to or lower than 5%. Any statistical tests will be two-sided. P-values will be presented. Where confidence limits can be estimated, the confidence level will be 95%. All analyses will be performed by intention to treat.

A chi-square test (or Fisher's exact test) will be performed on the primary outcome variable data (number of patients free of vertigo attacks at 12 months post-operatively, in EDB vs endolymphatic sac decompression group).

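### Section 4.4 credits Fisher's exact test with 80% power at 32 per arm; that figure fits the uncorrected chi-square, and Fisher's test has 68.0%

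*Protocol*

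**What the plan says.** Protocol section 4.4 (Sample size calculation) fixes every input to the power calculation. The success rates are 95% with the clip and 70% with decompression, "and with anticipated 25% percent difference", tested "with two-sided alternative hypothesis". The chance of a false positive "is controlled at the 5% level (family wise error rate"). The power target is stated as "Power is at least 80"%. The result is given as: "To obtain a power of at least 80% for Fisher's Exact test, the required sample size is 32 in groups A and B". Five per arm are added for loss to follow-up, giving 37 per arm and 74 in total. Missing outcomes are to be multiply imputed.

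Section 10.1 (Primary study parameter) gives the analysis: "A chi-square test (or Fisher's exact test) will be performed on the primary outcome variable data". It does not say when the bracketed test replaces the other.

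Section 8.5 says that the number of participants "takes into account that at least 15% of the participants in both arms of the study will drop out".

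**The concern.** Fisher's exact test is conservative in small samples, and 32 per arm is a small number for 80% power at 95% v 70%. If the result belongs to another test, section 4.4 misstates the chance of detecting the planned effect with the test it names. Section 10.1 does not settle the matter, because it allows either test and the two differ materially in power at this size. Every participant has ear surgery, so the justification of the sample size should be correct for the test that will decide the trial.

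**Working it through.** **Inputs, all from section 4.4:** success rates 0.95 and 0.70, two-sided 5%, equal arms, 32 per arm evaluable, 37 per arm randomised.

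**Method.** Let x and y be the numbers of successes in two arms of size n. Power is the sum, over all pairs (x, y), of Bin(x; n, 0.95) × Bin(y; n, 0.70), counting only the pairs that the test rejects at 5%. Fisher rejects when its two-sided exact p-value is at most 0.05. The uncorrected Pearson test rejects when z = (|x − y|/n) / √[2·p̄(1 − p̄)/n] is at least 1.96, with p̄ = (x + y)/(2n).

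**Step 1: where 32 comes from.** For the uncorrected Pearson test, exact power is 79.2% at 31 per arm and 80.6% at 32, so 32 is the smallest size that reaches 80%. Two approximations land nearby:
- Arcsine: h = 2·arcsin√0.95 − 2·arcsin√0.70 ≈ 0.708, and n = 2 × (2.802/0.708)² ≈ 31.3, which rounds up to 32.
- Unpooled normal: n = (0.95×0.05 + 0.70×0.30) × 2.802²/0.25² = 0.2575 × 7.849/0.0625 ≈ 32.3, which rounds up to 33.

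**Step 2: the test that section 4.4 names.**

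| Per arm | Fisher, two-sided | Pearson, uncorrected |
|---|---|---|
| 31 | 65.6% | 79.2% |
| 32 | 68.0% | 80.6% |
| 37 | 77.6% | 86.1% |
| 38 | 79.2% | 87.1% |
| 39 | 80.7% | 88.0% |

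Fisher falls 80 − 68.0 = 12 points short at 32 per arm. It is still below 80% with complete outcomes on all 37.

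**Step 3: readings that might rescue the statement.** At 32 per arm:
- mid-p Fisher: 73.9%
- one-sided Fisher at 5%: 78.3% (this also contradicts the stated two-sided test)
- two-sided Fisher with the 96.5% rate that section 4.4 quotes from the earlier trial: 76.5%

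None reaches 80%.

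**Step 4: Fisher as a fallback.** Section 10.1 gives no rule. Assume that Fisher is used only when an expected cell count is below 5, and Pearson otherwise. With equal arms the expected failure count per arm is half the total failures. Under the planned rates it falls below 5 in about 28% of trials at 32 per arm and 13% at 37. Power is then 74.4% at 32 and 83.6% at 37. At 32 per arm, the failures expected under the plan average (0.05 + 0.30) × 32/2 = 5.6 per arm. At 37 per arm they average 6.5.

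**Step 5: type I error.** At a common success rate of 82.5%, Pearson's exact size is 5.1% and Fisher's is 2.2% to 2.5%. Over common rates from 60% to 90%, Pearson's size reaches 5.6% at 32 per arm and 5.8% at 37.

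**Step 6: drop-out.** Five per arm is 5/37 = 13.5% of those randomised, or 5/32 = 15.6% of the evaluable number. Inflating the evaluable number gives 32 × 1.15 = 36.8, which rounds to 37. If 15% of those randomised drop out, 0.85 × 37 = 31.45 remain. Pearson power at 31 is 79.2%.

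**The case against.** The best defence is that section 10.1, which governs the analysis, puts chi-square first and Fisher in brackets. Under the uncorrected chi-square the planned size does what section 4.4 promises: 80.6% at 32 and 86.1% at 37. On that view the error is a label. This stands as a limit on the consequence. It does not make the sentence about Fisher's test true, and it holds only if chi-square is fixed as the primary test and used without continuity correction. The corrected version has 67.9% at 32.

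A reader might infer that the trial is under-sized, with a 32% chance of missing the planned effect. The documents do not support that as a general statement. It applies only if Fisher is used and only 32 per arm inform the result.

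A reader might also infer that the test is to be picked once the results are known. The protocol does not say so. The bracket is commonly read as a fallback for small expected counts, and an analysis plan could supply the trigger. What can be said is that section 10.1 gives no rule and that the choice affects power (Steps 2 and 4).

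The drop-out wording might be read as an arithmetic error that leaves the trial short. However, 15% fits an allowance taken on 32, the gap is about half a patient per arm, and section 4.4 plans imputation, so 31.45 is not simply the number analysed.

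**Conclusion.** The point holds as a misstatement in section 4.4. At 95% v 70% and two-sided 5%, Fisher's exact test does not have at least 80% power at 32 per arm, and 39 evaluable per arm are needed. The cause is not stated. The number 32 is what the uncorrected, unstratified Pearson test requires, so the result of one test has most likely been attached to the name of another.

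The size of the problem depends on the test finally used, from no shortfall with the uncorrected Pearson test to 12 points with Fisher at 32 per arm. The intermediate fallback figures rest on the assumed trigger of an expected count below 5. All figures for 37 per arm assume complete outcomes. Imputed outcomes carry less information, so power would then be lower. The figures also take the full 5% for this one comparison.

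**What to change.** Before unblinding, name one primary test, in the same words, in sections 4.4 and 10.1, and restate the power for that test. There are two direct options:

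- **Uncorrected Pearson chi-square.** Remove the open alternative and state 80.6% power at 32 evaluable per arm. This is a wording change with no extra patients. The price is that exact type I error can reach about 5.6% to 5.8% at some common rates between 60% and 90%, against the 5% control that section 4.4 promises, and this should be acknowledged.
- **Fisher's exact test.** State 68% at 32 per arm and 78% at 37. Type I error is then held below 5%, at the price of lower power. Keeping the 80% claim would need 39 evaluable per arm, or 39 + 5 = 44 per arm and 88 in total with the protocol's own allowance.

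If Fisher is wanted only as a fallback, write the trigger into section 10.1 and quote the power of the combined rule. With an expected count below 5 as the trigger, that is 74.4% at 32 and 83.6% at 37. The fallback should not be dismissed on the ground that counts will be large, given 5.6 expected failures per arm at 32.

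If a stratified test is adopted instead, compute its power separately and state that no continuity correction is applied. The 80.6% belongs to the unstratified test and cannot be carried over.

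Minor: in section 8.5, replace the 15% statement with the allowance actually made, 5 per arm, and say whether the percentage is of 37 randomised (13.5%) or of 32 evaluable (15.6%).
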